## 5.2 Analysis of secondary outcomes

### All-cause death, CV death and non-CV death

Event rates will be estimated using Kaplan-Meier methods, estimates of the treatment effect (HR) will be made using Cox regression models and reported with 95% CI's, as described above. The proportional hazards assumption will be assessed, and alternatives explored as previously described.

Competing risks analyses will be performed for the analysis of CV death, with non-CV death as the competing event, as per section 5.1.3. Cause-specific cumulative incidence curves will be provided for CV and non-CV death. In the case of non-proportional hazards alternative approaches will be explored, as previously described.

**Example Table: Primary and secondary time to event outcomes**

| Endpoint                        | Conservative strategy
no. events / no. patients (%) | Invasive strategy
no. events / no. patients (%) | Hazard Ratio‡
(95% CI) | p-value* |
|---------------------------------|---------------------------------------------------------------|-----------------------------------------------------------|---------------------------|----------|
| CV death or non-fatal MI        |                                                               |                                                           |                           |          |
| All-cause death or non-fatal MI |                                                               |                                                           |                           |          |
| All-cause death                 |                                                               |                                                           |                           |          |
| CV death                        |                                                               |                                                           |                           |          |
| Non-CV death                    |                                                               |                                                           |                           |          |
| Non-fatal MI                    |                                                               |                                                           |                           |          |
| Coronary angiography†           |                                                               |                                                           |                           |          |
| Coronary revascularisation†     |                                                               |                                                           |                           |          |
| Bleeding (BARC ≥2)              |                                                               |                                                           |                           |          |

†Not including trial angiography and revascularisation procedures

‡Adjusted for frailty

\*p-values will only be reported for the primary outcome

**Example Figure (simulated data): Kaplan-Meier estimates of the incidence of CV death or non-fatal MI**[figure not shown]

Similar Tables and Figures will be provided for all other time to event endpoints. Tables and Figures will also be provided to show cumulative incidence rates and sub-hazard ratios estimated via competing risks methodology.

#### Recurrent MI, coronary angiography, coronary revascularisation, stroke, TIA, hospitalisation for heart failure

For each outcome measure, the number of participants reporting the event, the number of events per participant, and the total number of events (including multiple events per participant) will be tabulated by randomised group. The crude rate (total number of events or total follow up time) will also be reported alongside 95% CIs.

Time to non-fatal MI, time to first (non-trial) coronary angiography and time to first (non-trial) revascularisation will be estimated using Kaplan-Meier methods. Estimates of the treatment effect (HR) will be made using Cox regression models, as described above and reported with 95% CI's. The proportional hazards assumption will be assessed, and alternatives explored as previously described. Competing risks analyses will also be performed with death as the competing event, as per section 5.1.3.

**Example Table: Occurrence of secondary outcome events**

|                                    | Invasive Strategy
(N=) | Conservative Strategy
(N=) |
|------------------------------------|---------------------------|-------------------------------|
| Total follow up             |                           |                               |
| Years                              |                           |                               |
| Recurrent MI                |                           |                               |
| Total [#pts (#events)]             |                           |                               |
| Non-fatal                          |                           |                               |
| Fatal                              |                           |                               |
| Total                              |                           |                               |
| No. per participant                |                           |                               |
| 1                                  |                           |                               |
| 2                                  |                           |                               |
| ≥3                                 |                           |                               |
| Type [#pts (#events)]              |                           |                               |
| Type 1                             |                           |                               |
| Type 2                             |                           |                               |
| Type 3                             |                           |                               |
| Type 4-5                           |                           |                               |
| Rate/100 person years (95% CI)     |                           |                               |
| Coronary angiography†       |                           |                               |
| Total [#pts (#events)]             |                           |                               |
| No. per participant                |                           |                               |
| 1                                  |                           |                               |
| 2                                  |                           |                               |
| ≥3                                 |                           |                               |
| Rate/100 person years (95% CI)     |                           |                               |
| Coronary revascularisation† |                           |                               |
| Total [#pts (#events)]             |                           |                               |
| No. per participant                |                           |                               |
| 1                                  |                           |                               |
| 2                                  |                           |                               |
| ≥3                                 |                           |                               |
| Rate/100 person years (95% CI)     |                           |                               |
| Stroke                      |                           |                               |
| Total [#pts (#events)]             |                           |                               |
| No. per participant                |                           |                               |
| 1                                  |                           |                               |
| 2                                  |                           |                               |
| ≥3                                 |                           |                               |
| Rate/100 person years (95% CI)     |                           |                               |
| TIA                         |                           |                               |
| Total [#pts (#events)]             |                           |                               |
| No. per participant                |                           |                               |
| 1                                  |                           |                               |
| 2                                  |                           |                               |
| ≥3                                 |                           |                               |

|                                          | Invasive Strategy
(N=) | Conservative Strategy
(N=) |
|------------------------------------------|---------------------------|-------------------------------|
| Rate/100 person years (95% CI)           |                           |                               |
| Hospitalisation for heart failure |                           |                               |
| Total [#pts (#events)]                   |                           |                               |
| No. per participant                      |                           |                               |
| 1                                        |                           |                               |
| 2                                        |                           |                               |
| ≥3                                       |                           |                               |
| Rate/100 person years (95% CI)           |                           |                               |
| Bleeding (BARC ≥2)                |                           |                               |
| Total [#pts (#events)]                   |                           |                               |
| No. per participant                      |                           |                               |
| 1                                        |                           |                               |
| 2                                        |                           |                               |
| ≥3                                       |                           |                               |
| Rate/100 person years (95% CI)           |                           |                               |
| BARC Type [#pts (#events)]               |                           |                               |
| Type 2                                   |                           |                               |
| Type 3a                                  |                           |                               |
| Type 3b                                  |                           |                               |
| Type 3c                                  |                           |                               |
| Type 4                                   |                           |                               |
| Type 5a                                  |                           |                               |
| Type 5b                                  |                           |                               |

*†Not including trial angiography and revascularisation procedures*

### Bleeding

The number of participants reporting a bleeding event, the number of events per participant, and the total number of events (including multiple events per participant) will be tabulated by randomised group. The crude rate (total number of events or total follow up time) will also be reported alongside 95% CIs. Data will also be summarised descriptively by BARC type/grade. A Kaplan-Meier plot will be used to show time to first bleed (BARC  $\geq 2$ ) by randomised group.

### Frailty scores

The distribution of scores over time will be summarised descriptively for each scoring instrument (Fried and Rockwood). Change in score from baseline and change in status (i.e. non-frail to frail) may also be summarised descriptively. Data will also be presented graphically.

### Length of time spent at home

The main place of residence will be tabulated in each treatment group at each visit.

A Kaplan-Meier plot will be used to show the time to moving to a residential or nursing home by randomised group.

## **5.3 Additional and exploratory analyses**

### **5.3.1 Sub-group analyses**

We will explore whether the treatment effect for the primary outcome measure is consistent across the following sub-groups:

- Frail versus not frail patients (Rockwood score  $\geq 5$  vs.  $< 5$ )
- Cognitively impaired versus not impaired (MoCA score  $< 26$  vs.  $\geq 26$ )
- Co-morbid (Charlson age comorbidity index  $> 5$ ) versus non co-morbid patients (Charlson age comorbidity index  $\leq 5$ )
- Age  $\geq 80$  vs  $< 80$  years
- Male versus female
- Diabetes versus no diabetes;
- Hypertension vs. no hypertension
- Grace  $> 140$  vs  $\leq 140$
- Renal disease vs. no renal disease
- Prior MI vs. no prior MI
- Never smoked vs smoked

Hazard Ratios of the treatment effect will be calculated within identified subgroups and displayed using a Forest plot with associated 95% confidence intervals. Interactions between the levels of each sub-group and the treatment effect will be evaluated with Wald tests used to assess the significance of the interaction.

As the trial has not been powered to detect subgroup effects, and no adjustment for multiplicity is planned, results from these analyses should be considered exploratory and not used to infer definitive treatment effects.

### 5.3.2 Additional and exploratory analyses

- At a joint meeting of the DMC/TSC on 4th May 2016, prior to the trial opening to recruitment, the committee noted that rates of type 4 and 5 MI may be different early in the follow-up period and consideration should be given on whether this should be accounted for in the analysis as it might mask the impact of more clinically significant MIs that occur. One approach to account for this is to perform a landmark analysis of the primary outcome as per the FAME 2 trial analysis. For this study a landmark (cut-off) point of 30 days from randomisation would be used to allow time for any CABG procedures to be performed. HRs pre and post the landmark time would be presented. Alternative methods may be explored.
- Each component of the composite primary endpoint will be explored using the win-ratio method. The main analysis of the primary outcome only takes the first event of the composite into account. However, this is often an event of lesser clinical importance, for example when a patient has a recurrent MI, whether they subsequently die is ignored. This method allows for clinical priorities, i.e. that CV deaths are considered more important than a recurrent MI, by first forming patients in the two treatment groups into matched pairs and then for each pair the invasive treatment is labelled a 'winner' or 'loser' depending on who had a CV death first. If that is unknown, then it will depend on who had a recurrent MI first. Otherwise, they will be considered ties. The 'win-ratio' is then the total number of winners divided by the total number of losers. Patients will be ranked and matched based on their risk profile (based on a risk score calculated from the coefficients of the adjusted Cox model for the primary outcome – excluding the treatment coefficient) and time stratified based on yearly intervals of the recruitment duration. The win-ratio will be presented with a 95% CI. This analysis will be strictly exploratory in nature.
- Further analyses may explore treatment effects in following additional subgroups, however it is not anticipated this will form part of the main trial report;
  - Fried frail vs prefrail vs robust
  - Frail and cognitively impaired patients versus non-frail, non-cognitively impaired patients
  - Diabetes and/or renal disease vs no diabetes and no renal disease
  - Impaired LV function vs. normal LV function (only in those with echocardiogram)
  - Severe (>50% stenosis in any epicardial vessel) vs. non-severe (<50%) coronary disease – based on angiographic analysis
  - Obstructive vs non-obstructive disease – based on angiographic analysis. This may also be explored by frailty and co-morbidity status

## 5.4 Missing data

Levels of missing data will be summarised. Withdrawals and losses to follow-up will be presented as described in section 4.4. Key baseline characteristics will be presented for the sub-population of participants who withdraw from the trial without allowing use of routinely collected data.

Most primary and secondary outcome measures are time to event endpoints. All participants will be included in the analysis of time-to-event outcomes, with participants who withdraw from the trial without allowing use of routinely collected data (and without prior non-fatal MI) censored at their last known follow-up time. We will primarily assume unobserved event times are censored at random, conditional on covariates included in the analysis model. However, for the primary outcome measure, if the proportion of participants (out of total randomised) censored due to withdrawal without use of routinely collected data is more than 5%, either overall or in either treatment group, we will perform sensitivity analyses using multiple imputation. We will follow the approach described by Jackson et al which will be implemented using the R package *InformativeCensoring*. Briefly, sensitivity analyses will be performed by assuming that, at the point of censoring, the hazard function is multiplied by a constant,  $e^\gamma$ . Where  $\gamma > 0$  there is an increased risk of failure after censoring, where  $\gamma < 0$  there is a reduced risk of failure after censoring, and  $\gamma = 0$  corresponds to the independent censoring assumption. By varying the value for  $\gamma$  we can assess the robustness of the censored at random assumption and find a 'tipping point' such that the conclusions of the trial would be altered.

The variables included in the imputation model will be the same as those included in the primary analysis model. We initially plan to impute 50 datasets, however this number may be increased if 50 imputations are not felt to provide adequate precision. Each imputed dataset will be analysed using the primary analysis model and Rubin's rules used to combine treatment effect estimates.

Event times will only be imputed for participants who withdraw from follow-up without allowing continued use of routinely collected data (and have not experienced a prior non-fatal MI). Event times will be capped at each participants maximum possible follow-up time, had they not withdrawn.

We initially plan to allow  $\gamma$  to vary between -3 and +3 in increments of 0.5, and find a 'tipping point' value for  $\gamma$  such that the conclusions of the trial would be altered. Extreme cases may also be considered, e.g. by assuming all censored participants in the conservative management arm would have an event immediately after censoring and all censored participants in the invasive arm would remain event-free until the end of the trial, and vice-versa. Sensitivity analyses using multiple imputation will only be considered for the analysis of the primary outcome measure.

## 6. SAFETY

### 6.1 Procedure-related complications

Procedural complications related to the study angiography or PCI will be tabulated. The number and proportion of patients experiencing a complication related to the study procedure will be reported descriptively alongside a 95% binomial confidence interval.

**Example Table: Frequency of procedural related complications**

|                                                                                                                          | Randomised to invasive management and undergoing angiography and/or PCI (N=) |        |
|--------------------------------------------------------------------------------------------------------------------------|------------------------------------------------------------------------------|--------|
|                                                                                                                          | N (%)                                                                        | 95% CI |
| Perforation                                                                                                              |                                                                              |        |
| Coronary Dissection                                                                                                      |                                                                              |        |
| Myocardial Infarction (type 4a)                                                                                          |                                                                              |        |
| TIA                                                                                                                      |                                                                              |        |
| Stroke                                                                                                                   |                                                                              |        |
| Need for renal replacement therapy                                                                                       |                                                                              |        |
| Death                                                                                                                    |                                                                              |        |
| >25% increase in serum creatinine concentration                                                                          |                                                                              |        |
| Aortic Dissection                                                                                                        |                                                                              |        |
| Cardiac tamponade                                                                                                        |                                                                              |        |
| Emergency repeat angiography or PCI                                                                                      |                                                                              |        |
| Procedure related pulmonary oedema                                                                                       |                                                                              |        |
| Vascular complications needing intervention                                                                              |                                                                              |        |
| Bleeding (BARC criteria)                                                                                                 |                                                                              |        |
| Type 2
Type 3a
Type 3b
Type 3c
Type 4
Type 5a
Type 5b |                                                                              |        |
| Other complication*                                                                                                      |                                                                              |        |
| Any complication                                                                                                         |                                                                              |        |

\*Other complications will be listed

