Other previous studies have been non-randomized retrospective sub-group analyses or in the setting of chronic stable angina.(20) Two published studies have thus far evaluated the benefit of invasive strategy versus conservative treatment in older ( $\geq 75$  years) patients with ACS without stratification for frailty status and recruiting selected patient cohorts with no significant co-morbidities. In the first registry study, 1005 patients underwent coronary angiography and revascularisation, and 931 patients received conservative treatment. The mean age was 79 and 82 years ( $p < 0.0001$ ) respectively. In-hospital mortality and the combined endpoint of death or non-fatal re-infarction were lower in patients undergoing invasive management compared to those being managed conservatively (6.0% vs. 12.5%,  $p < 0.0001$  and 9.6% vs. 17.3%,  $p < 0.0001$  respectively). There was a marked reduction in one-year mortality in the invasive treatment group compared to conservative treatment group (OR 0.56; 95% CI 0.38-0.81).(21) The second study randomized 313 patients  $\geq 75$  years old with NSTEMI or unstable angina to an early invasive approach ( $n=154$ ) or initial conservative approach ( $n=159$ ).(22) In the early invasive treatment group, 88% of patients underwent coronary angiography and 55% had PCI, and in the initial conservative group it was 29% and 23% respectively. In patients with NSTEMI, there was a reduction in the primary endpoint (composite of death, MI, stroke and rehospitalisation for CV causes) in the early invasive treatment group compared to conservative approach at 1 year (HR 0.43; 95% CI 0.23-0.80, Log rank  $p < 0.05$ ). There was no difference noted between the two groups with unstable angina.

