#### 9.2.2. Analyses of Secondary Outcome Measures

**Time to Event:** Analyses of secondary time to event outcomes will be analysed and reported using similar Kaplan Meier time to event analyses based on all-cause, cardiovascular and non-cardiovascular deaths. HRs of the risk of invasive treatment

compared with conservative therapy, adjusted for the stratification factor for level of frailty at randomisation, will be reported (with 95% confidence intervals).

Numbers and rates of recurrent myocardial infarction, hospitalisation (for heart failure), stroke, TIA, coronary angiography and coronary revascularisation and length of time spent at home will be reported descriptively.

**Safety data:** Comprising the numbers and rates of procedural complications (e.g. death, MI, major bleeding including gastrointestinal and intracranial bleeding [BARC definition],  $\geq 25\%$  increase in creatinine from baseline, need for renal replacement therapy, incidence of stroke or TIA) will be reported descriptively as frequency and proportions of the total number randomised to the invasive strategy and undergoing their allocated procedure (with 95% confidence intervals). Missing data are expected to be minimal and will be reported.

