| Criteria for coronary procedure-related myocardial infarction (types 4 and 5 MI)

Percutaneous coronary intervention (PCI) related MI is termed type 4a MI .
Coronary artery bypass grafting (CABG) related MI is termed type 5 MI .
Coronary procedure-related MI $\leq 48$ hours after the index procedure is arbitrarily defined by an elevation of cTn values $> 5$ times for type 4a MI and $> 10$ times for type 5 MI of the 99th percentile URL in patients with normal baseline values. Patients with elevated pre-procedural cTn values, in whom the pre-procedural cTn level are stable ( $\leq 20\%$ variation) or falling, must meet the criteria for a $> 5$ or $> 10$ fold increase and manifest a change from the baseline value of $> 20\%$ . In addition with at least one of the following: 
 
• New ischaemic ECG changes (this criterion is related to type 4a MI only);
 
• Development of new pathological Q waves;
 
• Imaging evidence of loss of viable myocardium that is presumed to be new and in a pattern consistent with an ischaemic aetiology;
 
• Angiographic findings consistent with a procedural flow-limiting complication such as coronary dissection, occlusion of a major epicardial artery or graft, side-branch occlusion-thrombus, disruption of collateral flow or distal embolization.
 
 Isolated development of new pathological Q waves meets the type 4a MI or type 5 MI criteria with either revascularization procedure if cTn values are elevated and rising but less than the pre-specified thresholds for PCI and CABG.
Other types of 4 MI include type 4b MI stent thrombosis and type 4c MI restenosis that both meet type 1 MI criteria.
Post-mortem demonstration of a procedure-related thrombus meets the type 4a MI criteria or type 4b MI criteria if associated with a stent. |

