### Procedural and in-hospital complications

Serious adverse events which are causally (possible, probable or definitely) related to the study angiography or PCI will be reported in patients randomised to the invasive arm undergoing their allocated coronary angiography procedure. Complications related to CABG will not be reported.

Expected procedure related complications include:

- Death
- Myocardial Infarction
- Minor (BARC<2) and major bleeding (BARC≥2)
- >25% increase in serum creatinine concentration from baseline
- Need for renal replacement therapy
- Coronary Dissection
- Aortic Dissection
- Coronary perforation
- Stroke
- TIA
- Cardiac tamponade
- Emergency repeat angiography or PCI procedure
- Procedure related pulmonary oedema
- Vascular complications needing intervention.

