### 3.3 Analysis populations

**Intention to treat (ITT):** This population contains all patients randomised into the study (regardless of whether they were later found to be ineligible, a protocol violator, not receiving the allocated treatment etc.).

**Safety population:** This population contains patients in the intervention group undergoing their randomised coronary angiography.

Analysis of the primary endpoint and all secondary endpoints (apart from procedural and in-hospital complications) will be conducted in the ITT population. Procedural and in-hospital complications will be presented in the safety population.

There will be some participants allocated to the invasive strategy who do not undergo their allocated procedure and some participants allocated to conservative management who go on to receive coronary angiography. However, any analysis in a per-protocol population, of participants receiving their allocated treatment strategy as per-protocol, is likely to be biased as treatment assignment would no longer be random and there would likely be an association between treatment switching and the risk of a clinical event. Furthermore, treatment switching reflects real-life clinical practice and a per-protocol analysis of participants receiving their allocated treatment as per-protocol would not estimate real-life clinical effectiveness. For these reasons, it is not planned to conduct any analyses in a per-protocol population of participants receiving their allocated treatment strategy.

A per-protocol analysis, excluding any participants found to be ineligible after randomisation, may be conducted as a sensitivity analysis if the number of ineligible patients is found to be excessive (>2.5%).

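### The SAP's procedural-complication table reports only type 4a MI, although the plan defines the complication as any MI related to the study angiography or PCI

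*Supplement*

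**What the plan says.** **Outcome definition.** SAP v2.0 section 2.4, under procedural and in-hospital complications, states: "Serious adverse events which are causally (possible, probable or definitely) related to the study angiography or PCI will be reported". This applies to invasive-arm patients who had their allocated angiography; CABG complications are excluded. Its list of expected complications contains "Myocardial Infarction" with no type attached. Protocol v3.0 also lists MI without a type in section 2.3.2 (secondary outcomes), section 8.4 (expected events within 7 days of angiography and/or PCI) and section 9.2.2 (safety data).

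**Reporting.** The text of SAP 6.1 asks for complications related to the study angiography or PCI to be tabulated with proportions and 95% binomial intervals. It does not restrict MI by type. The example table beneath it has one MI row, "Myocardial Infarction (type 4a", and one column, "Randomised to invasive management and undergoing angiography and/or PCI (N".

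**MI types.** Protocol 16.1 says: "Percutaneous coronary intervention (PCI) related MI is termed" type 4a. It names stent thrombosis (4b) and restenosis (4c) as separate types.

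**Denominator.** The safety population in SAP 3.3 reads: "This population contains patients in the intervention group undergoing their randomised coronary angiography". Protocol 9.2.2 likewise asks for "frequency and proportions of the total number randomised to the invasive strategy and undergoing their allocated procedure".

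**The concern.** The row label is narrower than the outcome it is meant to report. A complication that the plan names without restriction is reduced in the table to the one subtype that requires PCI. An analyst who follows the table would publish, as the trial's MI complication rate, a figure that excludes some of the events the plan says belong in it. Protocol 7.1.2 has a procedure-related MI risk below 1% quoted to patients, and this row is the trial's natural summary of that same risk. It should therefore count the same thing.

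**Working it through.** The plan states no rate for this complication, so there is nothing to reproduce. The check sets the definition against the table row.

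**1. Numerator under the definition (SAP 2.4).** D = patients in the safety population with an MI of any type judged possibly, probably or definitely related to the study angiography or PCI.

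**2. Numerator in the table (SAP 6.1).** A = patients in the same population with a type 4a MI.

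**3. What lies between them, K = D − A.**
- A related MI in a patient who had angiography but no PCI. SAP 2.1 makes revascularisation depend on the angiographic findings and on clinical discretion, so such patients are expected. Under protocol 16.1 their MI cannot be type 4a.
- An early stent-thrombosis MI after the study PCI. This can be causally related to the PCI, but protocol 16.1 classes it as type 4b.

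Neither has an MI row of its own. The only rows that can hold them are *Other complication* and *Any complication*, and the SAP does not say that MIs other than 4a go there.

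**4. Size of the gap.** Both versions use the same denominator N, so N cancels:

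share of defined MIs missing from the row = K / (A + K).

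Neither A nor K is given in the documents.

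**5. Illustration, with assumed counts.**
- The planned sample size of 1668 at 1:1 gives 1668 / 2 = 834 in the invasive arm.
- For the share having angiography, borrow the figure from an earlier trial in patients aged 75 or over, cited in the protocol background ("88% of patients underwent coronary angiography and 55% had PCI"): 834 × 0.88 ≈ 734. This is not a figure for the present trial.
- Assume A = 5, with no patient counted twice.

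| Other related MIs (K) | Table row, A/N | Defined rate, (A+K)/N | Share missing, K/(A+K) |
|---|---|---|---|
| 0 | 5/734 = 0.68% | 0.68% | 0% |
| 2 | 0.68% | 7/734 = 0.95% | 2/7 = 29% |
| 5 | 0.68% | 10/734 = 1.36% | 5/10 = 50% |

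The exact 95% interval printed beside the row would be 0.22% to 1.58% in all three cases, because it is computed on A alone.

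**The case against.** The strongest defence is that this is an example table, and that the governing text in SAP 6.1 and the definition in SAP 2.4 carry no type restriction. The label also has a plausible origin: protocol 16.1 gives troponin thresholds for procedure-related MI only for types 4a and 5, and CABG complications are excluded. The other events are recoverable too. *Other complication* is counted and itemised, *Any complication* covers everything, SAP 6.2 provides a line listing of each expedited event, and SAP 2.4 plans counts of every recurrent MI by type.

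Most of this stands and limits the weight of the point. A reader might infer that MIs of other types would vanish from the publication; the documents do not support that. What remains is that a named expected complication should not depend on a catch-all row. The by-type MI counts also do not replace the missing rate, since they cover both arms and all follow-up, whether or not the MI was related to the procedure.

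A stronger reading is also tempting: that the denominator is wrong because patients without PCI cannot have a type 4a MI. Using the earlier trial's figures, 55/88 = 0.625, so the row would be 1 − 0.625 = 37.5% too low. The documents do not support this as an error:
- The angiography denominator is chosen deliberately in protocol 9.2.2 and SAP 3.3.
- The row is nowhere called a per-PCI rate.
- That denominator suits a risk quoted to patients before angiography has shown whether PCI will follow.
- The 55/88 share belongs to another trial and assumes that every PCI there followed angiography.
- The number having PCI is reported under SAP 4.3.1, so a per-PCI rate can be worked out.

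Nor does this table drive the interpretation of early primary-endpoint MIs. SAP 5.3.2 provides a 30-day landmark analysis for that purpose.

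**Conclusion.** The point holds for the numerator only. The one MI row in the SAP 6.1 table is restricted to type 4a, while protocol 2.3.2 and 8.4 and SAP 2.4 define the complication without a type. Followed as written, the table gives an MI complication rate and confidence interval narrower than the defined outcome. The shortfall is K/(A + K): zero if every related MI is type 4a, and otherwise unknown until the data are seen. The 29% and 50% above rest on assumed counts and only show how the gap behaves.

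The denominator is sound. Severity is minor: the table is descriptive and covers one arm, the omitted events appear elsewhere in the planned output, and neither the primary analysis nor any comparison between arms is affected.

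**What to change.** In the SAP 6.1 table, relabel the row as myocardial infarction, any type, procedure-related. Give its count, proportion and 95% binomial interval over the existing safety-population denominator. Put the MI types beneath it as sub-rows, including 4a, as the table already does for bleeding by BARC type. CABG complications stay excluded, as SAP 2.4 provides.

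A type 4a rate among PCI recipients may be added, clearly labelled with its own denominator. This is optional presentation and not needed to resolve the inconsistency.

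The cost is an edit to one table. No new data are needed: relatedness is recorded for reported complications, protocol 8.4 has such MIs also entered as clinical endpoints, and SAP 2.4 and 4.3.1 already plan to report MI type and PCI receipt. The MI figure can only stay the same or rise.
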